#### Secondary outcomes

*Kessler-10 psychological distress scale* (K10) [33]*.* The K10 is a ten-item self-report measure designed to assess general (i.e. non-specific) psychological distress over the past 30 days. For the current RCTs, the time frame was modified to assess distress in the past two weeks. Items (e.g. ‘About how often did you feel hopeless?’) are rated on a 5-point scale ranging from 1 (none of the time) to 5 (all of the time). Total scores range from 10 (no distress) to 50 (severe distress). The K10 demonstrates strong psychometric properties in non-perinatal samples [39] and is advantageous for monitoring iCBT patients [40]. The K10 has also demonstrated acceptable sensitivity and specificity in identifying depression and some anxiety disorders in pregnant women [41].

*Edinburgh Postnatal Depression Scale* (EPDS) [42]. The EPDS is a ten-item self-report screening tool originally developed to detect symptoms of postpartum depression, although it is also used to assess for depression during pregnancy [43]. The EPDS enquires as to the intensity of symptoms over the past seven days (e.g. ‘I have felt sad or miserable’; ‘I have blamed myself unnecessarily when things went wrong’). Items are rated on a scale from 0 (e.g. no, not at all) to 3 (e.g. yes, most of the time), with a maximum total score of 30. A total score of > 12 is indicative of possible depression. The EPDS is well validated as a screening tool in antenatal and postpartum samples, with sensitivity in the range of 70–85% and specificity in the range of 77–85% in identifying a major depressive episode [20, 44, 45].

*World Health Organization Quality of Life* (WHOQOL-BREF) [46]. The WHOQOL-BREF is a 26-item self-report measure assessing quality of life (QOL) over the past four weeks. QOL is measured across four domains: physical health (e.g. sleep, pain); psychological health (e.g. self-esteem, concentration); social relationships (e.g. support; personal relationships); and environment (e.g. physical safety; financial resources). Items (e.g. ‘How much do you enjoy life?’) are rated on a 5-point Likert scale ranging from 1 (e.g. not at all) to 5 (e.g. an extreme amount). The WHOQOL-BREF has been validated in postpartum women, with satisfactory internal consistency and high discriminant validity [47]. The computerised version of the WHOQOL-BREF has demonstrated excellent psychometric properties [48].

*Maternal Antenatal Attachment Scale* (MAAS) [49]. The MAAS is a 19-item self-report measure designed to assess maternal feelings of emotional bonding to the fetus over the past two weeks. The scale has two domains indicating quality of maternal bonding (i.e. affective experiences such as closeness, tenderness); and intensity of preoccupation with the fetus (i.e. amount of time spent thinking about the unborn baby). All items are rated on a 5-point Likert scale ranging from 1 (low attachment) to 5 (high attachment). Total scores are in the range of 19–95, with higher scores indicative of better maternal attachment. The MAAS demonstrates acceptable internal consistency and construct validity in pregnant women [49, 50].

*Maternal Postnatal Attachment Scale* (MPAS) [51]. The MPAS is a 19-item self-report measure designed to assess maternal feelings of emotional bonding to the infant over the past two weeks. The scale has three domains indicating quality of attachment, absence of hostility towards the infant and pleasure in interacting with the infant. Items (e.g. ‘Over the last two weeks I would describe my feelings for the baby as…’) are rated on 2-, 3-, 4- and 5-point scales, with responses recoded to represent a score of 1 (low attachment, e.g. dislike) to 5 (high attachment, e.g. intense affection). Higher total scores are indicative of better maternal attachment. The MPAS has demonstrated acceptable levels of internal consistency, test–retest reliability and construct validity in postnatal women [51–53].

*Karitane Parenting Confidence Scale* (KPCS) [54]. The KPCS is a 15-item self-report questionnaire designed to measure perceived parental self-efficacy in parents with infants aged 0 and 12 months. ‘Task-specific’ items (e.g. ‘I can settle my baby’; ‘I am confident about playing with my baby’) are rated on a 4-point scale ranging from 0 (no, hardly ever) to 3 (yes, most of the time), with higher scores indicating higher parenting confidence. Total scores < 40 are indicative of lower than normal parenting confidence. The KPCS has been validated for use with mothers and demonstrates acceptable test–retest reliability (*r* = 0.88), internal consistency (Cronbach’s *a* = 0.81) and convergent and discriminant validity [54].

*Beck Depression Inventory, second edition* (BDI-II) [32]. The BDI-II is a 21-item self-report measure designed to assess the presence and severity of depressive symptom over the past two weeks and is based on DSM-IV criteria for MDD. Items are rated on a 3-point scale, with higher scores indicating more severe depression. The BDI-II possesses high internal consistency for psychiatric and non-psychiatric populations [32]. Only Question 9 (‘Suicidal thoughts or wishes: (0) I don’t have any thoughts of killing myself; (1) I have thoughts of killing myself, but I would not carry them out; (2) I would like to kill myself; (3) I would kill myself if I had the chance’) will be used to help determine suicidal ideation and suicide risk.

##### Treatment-relevant outcomes

Two items from the Credibility/Expectancy Questionnaire (CEQ) [55] will be used to assess expectancy of treatment benefit (e.g. ‘At this point, how logical does the program offered to you seem?’; ‘At this point, how successfully do you think this treatment will be in reducing your anxiety and/or depression symptoms?’). Items are rated on a 0 (not at all) to 9 (very much) scale and will be completed before Lesson 1 and Lesson 2. Treatment satisfaction will be assessed with 19 questions derived from the Treatment Satisfaction Questionnaire (TSQ) [56]. Items will enquire into the perceived helpfulness of the program (e.g. ‘How satisfied are you with the skills that this program has taught you to manage your symptoms of anxiety and/or depression?’; ‘What did you find most helpful/unhelpful?’; ‘How logical was the program?’), relatedness with characters (‘How much did you relate to the character Lee?’) and additional program feedback (e.g. ‘What could we do to improve the *MUMentum* program?’). Treatment adherence will be reflected in the mean number of CBT sessions viewed.

#### Description of iCBT programs

*MUMentum* was adapted from a six-lesson, guided iCBT program for anxiety and depression in the general population [25, 57]. Given women face many barriers to treatment engagement (e.g. time-poor; lack of treatment relevance to perinatal-related issues), the six-lesson transdiagnostic CBT program was divided into two brief courses focused on the antenatal or postpartum period with content presented over three lessons. Both *MUMentum* programs cover the same core principles and skills of CBT including psychoeducation, cognitive restructuring and problem-solving, behavioural activation and relapse prevention, with each lesson building upon the previous lesson (see Table 1). However, both courses differ in the context in which CBT skills are learned. The pregnancy course (*MUMentum Pregnancy*) is specifically tailored to women in the antenatal period and focuses on learning CBT skills in the context of character experiences, challenges and symptoms common during pregnancy (e.g. difficulties conceiving; increased anxiety surrounding the impending birth and health of the baby). In comparison, the postpartum course (*MUMentum Postnatal*) has been developed to target the unique issues, challenges and symptoms common during the postpartum period (e.g. asking for help; busting myths about motherhood; adjusting to changes in relationships; prioritising self-care; intrusive thoughts).

**Table 1 Tab1:** Core CBT skills of *MUMentum* programs

Lesson	Skills	Extra resources
1	• Psychoeducation: o About anxiety and depression o Identifying symptoms o Cognitive behavioural model o Prioritising self-care o Physical symptoms o Partners and supporters • Controlled breathing • Progressive muscle relaxation	• Medication for anxiety and depression during pregnancy and breastfeeding • Sleep hygiene • Fight-or-flight response • Pleasant activities • FAQs • Further skill examples
2	• Psychoeducation: o About thoughts o Identifying unhelpful thoughts o Shifting unhelpful thoughts o Accepting uncertainty • Thought challenging • Coping cards • Structured problem-solving	• Understanding intrusive thoughts and images • FAQs • Further skill examples
3	• Psychoeducation: o Unhelpful behaviours (low activity; avoidance) o Facing your fears • Activity planning and monitoring • Graded exposure • Assertive communication • Relapse prevention	• Self-care plan • FAQs • Further skill examples

Both programs are aimed as stand-alone, psychoeducational courses to introduce women to CBT skills to help manage symptoms of anxiety and depression. Content for each program is presented in the form of an illustrated story in which two fictional characters, who experience anxiety and depression, gain mastery over their symptoms with the help of a clinician (i.e. psychologist). Character stories for each program were developed with the key aim of being generalisable to a broad range of women and common experiences during pregnancy or postpartum (e.g. miscarriage; difficulties becoming pregnant; previous postpartum depression; traumatic birth, partner difficulties). Each lesson consists of: (1) a set of lesson slides depicting the characters story and use of CBT techniques (e.g. activity planning); (2) a lesson summary and action plan to review and implement the key topics and skills demonstrated in the slides; (3) and a range of supplementary resources (e.g. good sleep guide). A library of general resources is also available for participants to refer to throughout the program that cover additional information (e.g. emergency contacts; understanding medications for anxiety and depression during pregnancy and breastfeeding; information for partners and supporters) and further examples of key skills.

### Data management

All data will be collected and stored via the Virtual Clinic server. Any identifiable information collected remains confidential. Only members of the site (CRUfAD) research team will have access to participant information and identifiable data in order to monitor participant progress.

During data analysis, re-identifiable data (i.e. coded data) will be used. At study completion, non-identifiable data will be written to a password-protected database. All data will be extracted from the Virtual Clinic servers in the form of an Excel-compatible file to be transferred to the IBM Statistical Package for the Social Sciences (IBM SPSS, IBM Corp., Armonk, NY, USA) by a member of the research team.

Participants will be informed during the consent process at application that the research team plans to disseminate the trial results in peer-reviewed scientific publications and presentations. Participants are informed that in any such dissemination, their anonymity will be maintained. Participants will be sent (via email) a written summary of the results in lay terms following completion of the trial study phase.

### Statistical Methods

As there is limited research outlining the efficacy of iCBT for the treatment of perinatal anxiety and depression, power calculation of sample size (using ClinTools software) was informed by a published RCT of a transdiagnostic iCBT program [25]. To detect a between-group effect corresponding to Hedges’ *g* of 0.80, the minimum sample size for each group (alpha set at 0.05, power at 0.80) was identified as 25 per group. At least 10% more will be recruited to account for expected attrition.

All analyses will be conducted at conclusion of the trial when the desired sample size has been obtained. All analyses will be conducted using Statistical Package for the Social Sciences (IBM SPSS, IBM Corp., Armonk, NY, USA). Significance testing of group differences regarding demographic data and pre-treatment measurements will be conducted using analysis of variance (ANOVA) and Chi square (χ2) where the variables consist of nominal (or categorical) data.

Intent-to-treat (ITT) mixed models using restricted maximum likelihood (REML) estimation will be used to account for missing data due to participant dropout. Mixed models do not assume that the last measurement is stable (the last observation carried forward assumption) [58]. REML models are appropriate for RCTs with multiple time-points and pre- to post-only designs [59]. The assumption that data are missing at random will be evaluated using binary logistic regression to predict dropout and by comparing these two groups (those with missing data to those with complete data) on baseline measures. Significant effects will be followed up with pairwise contrasts comparing mean post-treatment (and follow-up) scores between groups. Effect sizes will be calculated between groups (Hedges’ *g* to account for small sample size) and within groups (Cohen’s *d*, adjusting for the repeated measures correlation) using the pooled standard deviation and adjusted for sample size. Post-hoc exploratory mediation analyses, using the PROCESS syntax for SPSS PROCESS [60], will be used to examine the associations between symptom change and changes in the maternal factors of mother–infant bonding, parenting confidence and maternal quality of life.

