#### Randomisation and allocation procedures

Online applications meeting the study’s inclusion criteria will be randomised to either iCBT or a TAU control group according to a 1:1 ratio within blocks of 20. Because the two trials were conducted using different software, the randomisation procedure differs slightly between the studies.

For study 1, the allocation sequence will be generated by an independent person not involved in the study, using a random number generator (https://www.random.org/). The numbers corresponding to the treatment group (1 = iCBT) or the control group (2 = TAU) will be placed in sequentially numbered, sealed opaque envelopes. The randomisation envelopes will then be assigned manually (by the study coordinator) to the successful online application in order of application date. Once matched, the group allocation will be revealed and participants will be notified of their group allocation by e-mail.

For study 2, which will be conducted in an updated Virtual Clinic web system,^1^ the randomisation sequence will be electronically uploaded to the server by an independent person not involved in the study. Successful applicants will be notified via e-mail of their acceptance into the study and automatically randomised to treatment group (1 = CBT) or control group (2 = TAU).

Once randomised, participants and research personnel will not be blinded to group condition. Participants in the intervention group and control group will login to https://virtualclinic.org.au/ and complete baseline (pre-treatment) questionnaires. The three primary data collection points for study participants in iCBT group and TAU group are as follows: baseline (pre-treatment), post treatment, and at one-month follow-up (see Fig. 2). Participants will receive notifications and reminders to complete questionnaires via computer-generated emails, SMS and follow-up phone calls from the research team. We will track reasons for non-adherence (e.g. lost to follow-up). As this is an unguided program, participant enquiries (e.g. technical issues) will be responded to by research technicians; no coaching or support with program content will be provided.

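### The between-group contrasts wait on unnamed significant effects and state no baseline adjustment; one direct, baseline-adjusted post-treatment test would gain power at no cost

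*Protocol article*

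**What the plan says.** All the statements come from the protocol article.

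- **Sample size (Statistical Methods).** The target is set as follows: "To detect a between-group effect corresponding to Hedges’ *g* of 0.80", and "the minimum sample size for each group (alpha set at 0.05, power at 0.80) was identified as 25 per group". For dropout: "At least 10% more will be recruited to account for expected attrition".
- **Analysis (Statistical Methods).** Intention-to-treat mixed models fitted by REML, and then: "Significant effects will be followed up with pairwise contrasts comparing mean post-treatment (and follow-up) scores between groups". The text does not say which effects count, or whether baseline enters as a covariate or as a repeated outcome.
- **Time-points (Randomisation and allocation procedures).** There are three: "baseline (pre-treatment), post treatment, and at one-month follow-up". The same section has women complete the baseline questionnaires after allocation, when they are no longer blinded.
- **Screening (Inclusion criteria; Online application and psychological assessment).** PHQ-9 and GAD-7, the two co-primary scales, are also completed at application, before randomisation.
- **Role of follow-up (Abstract).** The one-month assessment is there to show whether gains are maintained.

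**The concern.** The test that was sized and the test that is described do not match. The calculation assumes one comparison of two group means. The analysis has two stages: some model effect must reach significance, and only then are group means compared at post-treatment and follow-up.

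Two things are at stake. First, if the preliminary effect is one that involves group, a woman-level benefit of the planned size can be present at post-treatment and still go undeclared because the first stage failed. Second, every woman supplies a starting score on both co-primary scales, and a contrast that ignores it is less precise than it could be. With about 25 women per arm expected at analysis, and each study standing alone, neither loss is worth accepting when only wording is needed to avoid it.

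**Working it through.** **Inputs.** From Statistical Methods: standardised difference 0.80, alpha 0.05, power 0.80, 25 per group. Allocation is 1:1. Sidedness is not stated; two-sided is assumed, because one-sided gives 20 per group. The correlation r between time-points is not given, so a range is shown. Adding 10% gives 25 × 1.1 = 27.5, so 28 per group; a 10% loss leaves 28 × 0.9 ≈ 25.

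**1. The plan's own figure.** n per group = 2(1.960 + 0.842)² / 0.80² = 2 × 7.85 / 0.64 = 24.5, so 25. This reproduces the stated number as an unadjusted two-group comparison. Its power at 25 per group is 0.81 by the normal formula and 0.79 by the noncentral t.

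**2. Adjusting for baseline.** Adjustment multiplies the SD by √(1 − r²), so the effective difference is 0.80/√(1 − r²). At r = 0.5 this is 0.80/0.866 = 0.92. The t-based formula with 47 degrees of freedom gives power 0.83, 0.89, 0.93 and 0.97 at r = 0.3, 0.5, 0.6 and 0.7. Simulation, which also charges for chance baseline imbalance, gives 0.82, 0.88 to 0.89, 0.93 and 0.97. Against 0.79 unadjusted, the gain is about 3, 9 to 10, 14 and 18 percentage points.

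A mixed model does not supply this gain automatically. With complete data, baseline as a repeated outcome and a free baseline mean in each group, the post-treatment contrast equals the unadjusted difference.

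**3. Making the contrast conditional.** Simulation: 25 per arm, complete data, equal correlations, each test at 0.05, true post-treatment effect 0.80. The entries are the probability that the first-stage test and the unadjusted post-treatment contrast are both significant. The follow-up effect is either maintained at 0.80 or halved to 0.40. Small differences reflect the form of the interaction test and simulation error.

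| First-stage test | Follow-up effect | r = 0.3 | r = 0.5 | r = 0.6 | r = 0.7 | r = 0.8 |
|---|---|---|---|---|---|---|
| Group-by-time, 2 df | maintained | 0.55–0.58 | 0.66–0.68 | 0.72–0.74 | 0.76–0.78 | 0.79 |
| Group-by-time, 2 df | halved | 0.48–0.50 | 0.59–0.61 | 0.66–0.68 | 0.73–0.74 | 0.78–0.79 |
| Group main effect | maintained | 0.65–0.66 | 0.59–0.60 | 0.57 | 0.54 | 0.51 |
| Group main effect | halved | 0.46 | 0.39 | 0.36–0.37 | 0.34 | 0.32 |
| Any of group, time, interaction | maintained | 0.78 | 0.79 | 0.79 | 0.80 | 0.79 |
| Any of group, time, interaction | halved | 0.75 | 0.77 | 0.78 | 0.79 | 0.79 |

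The last two rows assume no improvement over time in the control group. With a shared improvement of 0.5 SD the loss in the last row disappears.

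**4. The interaction as the efficacy test by itself.** With the effect maintained, its power is about 0.67, 0.81 to 0.82, 0.90 and 0.96 at r = 0.3, 0.5, 0.6 and 0.7. With the effect halved at follow-up it is about 0.53, 0.68 to 0.69, 0.79 and 0.90.

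**The case against.** A reader might infer that the trial's power is well below 0.80 and that the missing baseline adjustment is a cause. The article does not support that. The 25 per group is itself the size for an unadjusted comparison, and that comparison delivers the stated power.

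A reader might also infer that the two-stage procedure certainly costs power. That needs three things the article does not state: that the first stage is a test involving group, that both stages must succeed, and, for the interaction, that the correlation is low to moderate. The Abstract says that efficacy is judged from the mixed models, which allows the interaction to be the efficacy test and the contrasts to be description. That test uses change from baseline, and with the effect maintained it reaches 0.80 from r of about 0.5. Counting success at either time-point also raises the figure: behind the interaction test, with the effect maintained, it is about 0.75 to 0.76 at r = 0.5 and 0.82 at r = 0.6. All of this stands, and it removes any claim of a fixed loss.

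It can be said too that model terms are detail an article leaves to a fuller plan. That is fair for the list of terms. It does not cover the sentence the article does contain, which makes the between-group comparison depend on an earlier significant result. Nor does the most lenient reading rescue that condition: a significant time effect, which keeps the loss small, says nothing about iCBT against usual care.

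**Conclusion.** The point holds as a mismatch and a missed gain. The sample size is for one direct unadjusted comparison; the analysis makes that comparison conditional on effects it does not name and states no baseline adjustment for it.

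The size of the gain is power of about 0.82 to 0.97 in place of 0.79, for r between 0.3 and 0.7. That rests on an assumed correlation within the enrolled sample, complete data and a true effect of 0.80. The entry rules restrict the range of the screening scores, which may hold r towards the lower end.

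The cost of the condition cannot be fixed from the article. It is small if any model effect suffices. If the group-by-time test and the post-treatment contrast must both be significant, power is about 0.56 to 0.79 for r from 0.3 to 0.8 with the effect maintained, and 0.48 to 0.78 if it halves by follow-up. This is a worthwhile clarification and a free improvement to the analysis; it does not show that the trial is underpowered.

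**What to change.** In Statistical Methods, for each co-primary outcome (PHQ-9 and GAD-7):

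- Name the baseline-adjusted group difference at post-treatment, estimated from the REML mixed model, as the primary test. Fit post-treatment and follow-up as outcomes, with group, time, group-by-time, and the covariate with its interaction with time.
- State that this test is performed directly and does not depend on any omnibus effect.
- Use the pre-randomisation screening score as the covariate, because the baseline questionnaires follow unblinded allocation. The gain depends on how well that screening score correlates with the outcome.
- Make the one-month contrast secondary, in line with its stated role of showing maintenance.
- Keep the planned pooled SD for Hedges' g. The baseline SD would be a poor denominator, since women are selected on these same scales and its range is restricted.
- Say that 25 per group was derived for the unadjusted comparison and is therefore conservative for the adjusted one whenever the covariate is usefully correlated with the outcome.

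The cost is wording only: no new data, no extra participants and the same software. The article reports that recruitment was still open and that all analyses wait until the trial ends, so as of that report the change could be made before any outcome analysis.
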